### Interim analyses {21b}

Not applicable, no interim analyses are needed to be performed.

### Methods for additional analyses (e.g. subgroup analyses) {20b}

Not applicable, no subgroup analyses will be performed.

### Methods in analysis to handle protocol non-adherence and any statistical methods to handle missing data {20c}

Missing data due to follow-up will be dealt with using multiple imputation according to the Markov-chain Monte Carlo method in cases of missing data (completely) at random, and we will additionally perform a sensitivity analysis using the Last Observation Carried Forward method.

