### Outcomes {12}

The primary outcome is the effect of early ICU-VR on psychological well-being, expressed as symptoms of PTSD, anxiety and depression and quality of life up to 6 months after hospital discharge. Secondary outcomes are, firstly, the intra-group changes in psychological well-being and quality of life and the inter-group differences in psychological well-being and quality of life during follow-up up to 12 months after hospital discharge, and secondly, patients’ satisfaction with and rating of ICU care and aftercare and patients’ perspectives on ICU-VR.

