### Participant timeline {13}

Figure 2 depicts participants’ recruitment and randomization, the study procedures and the outcomes of the study. Patients admitted for COVID-19 to the ICU of the participating hospitals will be invited to a post-COVID-19 outpatient clinic 3 months after hospital discharge as part of the regional standard of care. All patients will receive an information letter and will be contacted by telephone to discuss participation 1 month prior to this visit. During the outpatient clinic visit, informed consent will be obtained and patients will be randomized. Patients randomized to the early ICU-VR group will receive ICU-VR during the same visit, whereas patients randomized to the late ICU-VR group will receive ICU-VR during a second outpatient clinic visit 3 months later (i.e. 6 months after hospital discharge). Questionnaires will be sent at 3 months (prior to the first outpatient clinic visit), 4 months, 6 months (prior to the second outpatient clinic visit for patients in the late intervention group), 7 months and 12 months after hospital discharge.

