### Sample size {14}

In the previously conducted pilot study examining the feasibility, safety and clinical relevance of ICU-VR in sepsis survivors, we identified an effect size Cohen’s *d* of 0.77 [33]. Due to the non-normality of PTSD scores after 6 months, these calculations could represent an overestimation of the sample size. We consider the effect estimates for the ICU-VR module to be similar to the intervention group, as was tested in our pilot study. A G*Power analysis revealed that 80 patients have to be included in the study to detect such an effect size, using a two-sided alpha of 0.05, a power of 0.80, a 1:1 randomization and an expected loss to follow-up of 20% based on our pilot study. We will include patients from June 2020 to December 2020. When the minimum required number of patients is reached prior to December 2020, inclusion will be continued until December 2020. When the minimum required number of patients is not reached in December 2020, inclusion will be continued until the minimum required sample of 80 patients is reached.

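### LOCF, the only missing-data sensitivity analysis named, carries pre-ICU-VR scores past the intervention for patients with no later questionnaire, and departs from missing at random at only one point

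*Protocol article*

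**What the plan says.** Section {20c} of the protocol article, on non-adherence and missing data, gives the method as "multiple imputation according to the Markov-chain Monte Carlo method in cases of missing data (completely) at random". It then states that "we will additionally perform a sensitivity analysis using the Last Observation Carried Forward method". The article names no other sensitivity analysis for missing data. The sample-size section {14} allows for "an expected loss to follow-up of 20% based on our pilot study" and does not say when during follow-up the loss is expected.

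The order of questionnaire and intervention is in the participant timeline {13}: "Questionnaires will be sent at 3 months (prior to the first outpatient clinic visit), 4 months, 6 months (prior to the second outpatient clinic visit". That second visit concerns the late group only, and further questionnaires follow at 7 and 12 months. On the intervention, "Patients randomized to the early ICU-VR group will receive ICU-VR during the same visit", while the late group "will receive ICU-VR during a second outpatient clinic visit 3 months later (i.e. 6 months after hospital discharge"). The outcomes section {12} defines the primary outcome as the effect of early ICU-VR, "expressed as symptoms of PTSD, anxiety and depression and quality of life up to 6 months after hospital discharge".

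**The concern.** A sensitivity analysis for missing data should show how far the result depends on the assumption behind the main analysis, here that data are missing (completely) at random. LOCF does this poorly, for three reasons.

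- **Timing.** The last score before the intervention is taken immediately before it, so carrying that score forward assigns a patient who received ICU-VR an outcome measured without it.
- **Uncertainty.** Filled-in values enter the models as if they had been observed, whereas multiple imputation allows for their being unknown.
- **Information.** LOCF replaces the main assumption with a single alternative that cannot be varied. Its result cannot be read as a distance from the point where the conclusion would change.

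What is at stake is how the main result is interpreted. Patients report their own outcomes and know their allocation, so loss that depends on unobserved distress is a reasonable possibility to examine. LOCF could make a sound positive result look fragile. With unequal loss and natural recovery, it could also lend support to a difference that is not there.

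**Working it through.** **Inputs from the article.** Effect size d = 0.77, two-sided alpha 0.05, power 0.80, 1:1 allocation, 20% loss and N = 80 (Sample size {14}). No distribution was assumed (Limitations). Questionnaire and intervention times are from Participant timeline {13}.

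**The plan's own figure.** Section {20c} contains no number. The N of 80 reproduces with a Wilcoxon-Mann-Whitney calculation at the minimum relative efficiency of 0.864, which fits the statement that no distribution was assumed: 32 per arm, 64 in total, 64 / (1 − 0.20) = 80. A two-sample t-test would give 28 per arm and 56 / 0.80 = 70. The 80 stands, and nothing below changes it.

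**Which score is carried where.**

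| Patient | Last questionnaire | Filled in by LOCF | Score carried is |
|---|---|---|---|
| Early | 3 months | 4, 6, 7, 12 | pre-ICU-VR |
| Early | 4 months | 6, 7, 12 | post-ICU-VR |
| Late | 3 or 4 months | 6 and later | pre-ICU-VR; at month 6 the arm is still untreated |
| Late | 6 months | 7, 12 | pre-ICU-VR |

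Within the primary window, only the first row puts an untreated score at a treated time.

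**Effect at 6 months.** Let fE and fL be the shares of the early and late arms with no score after month 3, d the true effect and g the natural recovery from month 3 to month 6, both in SD units. LOCF sets the change of lost patients to zero, so the expected difference is

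(1 − fE)(d + g) − (1 − fL)g = (1 − fE)d + (fL − fE)g.

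The first term is dilution. The second is bias from unequal loss. The article gives neither the timing of loss nor g, so the values below are assumptions.

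Equal loss in both arms, d = 0.77 (g cancels):

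| Lost straight after month 3 | LOCF difference |
|---|---|
| 5% | 0.95 × 0.77 = 0.73 |
| 10% | 0.90 × 0.77 = 0.69 |
| 15% | 0.85 × 0.77 = 0.65 |
| 20% | 0.80 × 0.77 = 0.62 |

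Unequal loss, g = 0.4:

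- No true effect, 10% early and 30% late: (0.30 − 0.10) × 0.4 = +0.08 SD. With the losses reversed: −0.08 SD.
- d = 0.77, 10% early and 30% late: 0.90 × 0.77 + 0.08 = 0.77. The two errors cancel.
- d = 0.77, 30% early and 10% late: 0.70 × 0.77 − 0.08 = 0.46.

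The bias has no fixed sign, so LOCF cannot be defended as conservative.

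**What a graded analysis would show.** Suppose 20% are missing and the imputed early-arm scores are made worse by delta. The difference is then 0.77 − 0.20 × delta: 0.77 at delta 0, 0.73 at 0.2, 0.67 at 0.5, 0.62 at 0.77 and 0.57 at 1.0. LOCF under 20% equal loss yields only the 0.62, which matches a delta equal to the whole effect. A range that stopped at 0.5 would thus be a milder check than LOCF. If the same delta is applied to both arms, the difference moves by (fL − fE) × delta, so that version matters only when loss is unequal.

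**The case against.** The strongest reply is that LOCF is only an additional analysis. Multiple imputation and the mixed models supply the main result, and LOCF cannot alter that estimate. This stands and limits the weight of the point.

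It also rules out a tempting inference about power. With 20% lost straight after month 3 and 40 per arm, LOCF would reject in about 76% of trials, or 73% to 74% with 0.4 SD of natural recovery as well. A reader might set this against the planned 80% and conclude that the trial is underpowered. The documents do not support that: the 80% belongs to the planned comparison, and a sensitivity analysis has no power target.

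Other stronger readings also fail:

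- **That LOCF does not test missing at random at all.** It does depart from that assumption, in one fixed way, and under 20% equal loss the departure is fairly severe. The fair criticism is that the point is single and arbitrary.
- **That every lost patient contributes an untreated score.** An early patient who answers at month 4 carries a treated score forward, and the late arm is affected only after the primary window.
- **That 0.62 SD is the expected result.** The 20% is total loss with no timing given. If 5% to 10% go straight after month 3, the figure is 0.73 to 0.69.
- **That spurious findings are likely.** Simulating the 0.08 SD scenario raises false rejection only from about 5% to about 6%, and its inputs are not in the article.
- **That patients upset by ICU-VR will be the ones lost.** The article reports ICU-VR as safe, plans telephone contact to improve completion and records reasons for discontinuation. Informative loss is possible, but not shown.

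Finally, the unseen full protocol or analysis plan may contain a further analysis under missing not at random. The point therefore does not rest on its absence. It rests on LOCF being the check that the article itself fixes.

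**Conclusion.** The point holds as a weakness in a stated secondary method. The questionnaire schedule makes LOCF place pre-intervention scores at post-intervention times: at months 4 and 6 for early patients with no questionnaire after ICU-VR, and at months 7 and 12 for late patients with none after theirs. LOCF also understates uncertainty and offers one ungraded alternative to the main assumption.

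For a true 0.77 SD, the dilution ranges from 0.04 SD (5% lost straight after month 3) to 0.15 SD (20%), assuming equal loss in both arms. With 10% v 30% loss and 0.4 SD recovery, unequal loss adds about 0.08 SD in either direction. The timing of loss, the imbalance and the recovery are all assumptions. The main estimate and the sample size are not called into question. This should be changed, but it does not threaten the validity of the trial.

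**What to change.** In section {20c}, replace LOCF as the sensitivity analysis with delta-adjusted multiple imputation built on the imputations already planned. If LOCF is kept because it was pre-specified, label it a supplementary report.

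- Add a worsening of delta to the imputed scores, first in the early arm alone and then in both arms, with the sign set so that delta is a worsening on every scale.
- Take delta from 0 far enough to find the value at which the conclusion changes, and at least to about 0.8 SD, so that the range includes the LOCF-equivalent point of 0.77.
- Report that tipping point for the 6-month primary outcomes, including IES-R and HADS, since the article names several and no single lead.
- To keep the analyst blinded, apply the one-arm shift to each coded arm in turn.

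The cost is a few lines of code, a stated range for delta and slightly longer reporting. Sample size, visits and trial conduct do not change. As recruitment has closed, the change should be dated and made before the analyst learns which code is which arm.

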### Plans to give access to the full protocol, participant level-data and statistical code {31c}

The full protocol, participant-level dataset and statistical code will be available from the corresponding author on reasonable request.

## Oversight and monitoring

### Composition of the coordinating centre and trial steering committee {5d}

The principal investigators of each study site are responsible for the conduct of the study and day-to-day operations. The trial steering committee has designed the study and consulted a psychologist and psychiatrist for this purpose. One member of the trial steering committee has weekly meetings with the principal investigators of each study site. The trial steering committee is responsible for the continuation of the study, ensuring that the study protocol is followed at each study site, for data collection and for amendments of the study protocol, if necessary. All data will be validated by two members of the trial steering committee. All analyses will be performed by a member of the trial steering committee and will be checked by the statistician of the trial steering committee. The trial steering committee will meet once a month to discuss study progress.

### Composition of the data monitoring committee, its role and reporting structure {21a}

This study has negligible risks for patients. ICU-VR in a non-COVID-19 setting has previously been tested safe [32, 33]. Therefore, no data monitoring committee is needed.

### Adverse event reporting and harms {22}

Adverse events (AEs) reported by the participants or observed by the investigators will be recorded. Serious adverse events (SAEs) will be reported the principal investigator without undue delay after obtaining knowledge of the events. The principal investigator will report the SAE to the medical ethics committee of the Erasmus MC within 7 days of first knowledge for SAEs that result in death or are life-threatening, followed by a period of 8 days to complete the initial preliminary report. All other SAEs will be reported within a period of maximum 15 days after the investigator has first knowledge of the SAE. All AEs will be followed until they have abated, or until a stable situation has been reached. Depending on the event, follow up may require additional tests or medical procedures as indicated and/or referral to the general physician or a medical specialist. SAEs need to be reported till the end of study within the Netherlands

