### Relevant concomitant care permitted or prohibited during the trial {11d}

Participants randomized to the late ICU-VR group require an additional visit to an outpatient clinic to receive ICU-VR. No additional alterations to usual care pathways, including the use of any medication, are required for participants in this study.

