## Assignment of interventions: blinding

### Who will be blinded {17a}

Due to the nature of the intervention, neither the patients nor the investigator can be blinded to the randomization allocation. The allocation data within the dataset will be presented as either ‘0’ or ‘1’, without the corresponding randomization allocation. Thereby, the investigator performing the analysis will be blinded to the randomization allocation.

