Patients’ satisfaction with and rating of ICU care and aftercare was based on the Patient Satisfaction Questionnaire and Family Satisfaction with ICU Care tools, altered to the needs of this study [43–45]. Additional novel items were added to evaluate patients’ perspectives on the ICU-VR intervention.

This questionnaire comprised 21 items, categorized in four sections: (1) satisfaction with and rating of ICU care and ICU aftercare and the added value of ICU-VR; (2) overall perspectives on the ICU-VR intervention; (3) perspectives on the content of ICU-VR; and (4) perspective on the effect of ICU-VR. Questions regarding ICU-VR were only answered by patients who had received the intervention, questions regarding satisfaction and rating by all patients. Psychological well-being and health-related quality of life will be assessed at 3, 4, 6, 7 and 12 months after hospital discharge. Satisfaction with and rating of ICU care and aftercare and perspectives on ICU-VR were administered by telephone during the study period after the first outpatient clinic visit. Baseline demographics and treatment-related characteristics, including, but not limited to, age, gender, race, pre-existing comorbidities, hospital and ICU length of stays, mechanical ventilation-related data (duration, prone positioning, highest PaO_2_/FiO_2_ ratio, occurrence of delirium, sedation, illness severity scores (APACHE IV, SAPS II)), mortality and medication, will be retrieved from electronic patient records.

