### Plans to promote participant retention and complete follow-up {18b}

Patients will be contacted by telephone when a questionnaire needs to be filled in to improve follow-up completion. If a participant decides to discontinue their participation, the reason for the discontinuation will be recorded.

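### Adverse events for months 3 to 6 are gathered through unequal contact in the two arms with no common enquiry stated, so between-arm counts may be biased, by an unknown amount and in an uncertain direction

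*Protocol article*

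**What the plan says.** The section on adverse event reporting and harms gives the capture rule: "Adverse events (AEs) reported by the participants or observed by the investigators will be recorded". It sets reporting times for serious events, which are reportable until the end of the study without distinction by arm. It states no scheduled adverse-event enquiry.

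Contact with the study team differs by arm. Under the participant timeline, "Patients randomized to the early ICU-VR group will receive ICU-VR during the same visit", that is, at month 3. Late patients "will receive ICU-VR during a second outpatient clinic visit 3 months later (i.e. 6 months after hospital discharge". The section on concomitant care confirms that this visit belongs to one arm: "Participants randomized to the late ICU-VR group require an additional visit to an outpatient clinic to receive ICU-VR". No visit after month 3 is stated for the early arm.

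Other contact is common to both arms. The retention section says "Patients will be contacted by telephone when a questionnaire needs to be filled in to improve follow-up completion", and the assessment section says "Psychological well-being and health-related quality of life will be assessed at 3, 4, 6, 7 and 12 months after hospital discharge". The assessment section also describes a questionnaire on satisfaction and perspectives, given by telephone after the first clinic visit. Everyone answers its satisfaction items, but only patients who have had ICU-VR answer the items about it.

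The trial is open label: "neither the patients nor the investigator can be blinded to the randomization allocation". There is no data monitoring committee, because risk is judged negligible on the basis of ICU-VR used outside COVID-19.

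**The concern.** Both stated routes, participant report and investigator observation, depend on opportunity. During months 3 to 6 the early arm has had ICU-VR and the late arm has not, which makes this the only randomized comparison with untreated patients. The late arm then has a scheduled face-to-face contact at the end of that period and the early arm has none. Blinding cannot even this out, since patients and investigators know the allocation.

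Safety information on this version of the intervention is what is at stake. The trial adds new content (prone ventilation, tracheostomy, isolation measures) and gives it 3 months after hospital discharge, whereas the previous study applied ICU-VR about 8 days after ICU discharge. With no monitoring committee, recorded adverse events are a main source of evidence on whether the negligible-risk premise holds here. Counts that partly reflect the visit schedule support that premise poorly, whichever way they lean.

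**Working it through.** The plan gives no adverse-event rate, detection rate or event-based figure, so there is no figure of its own to reproduce. The check sets the stated capture opportunities side by side and then shows what would decide the size of any bias.

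**Step 1. Opportunities for recording events of months 3 to 6**

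| Opportunity | Early arm | Late arm |
|---|---|---|
| Month 3 visit | Includes the ICU-VR session | No ICU-VR session |
| Study visit after month 3 | None stated | One, at month 6 |
| Questionnaire calls, months 4 and 6 | Yes | Yes |
| Telephone satisfaction questionnaire | Yes, with ICU-VR items | Yes, without ICU-VR items until ICU-VR is received |
| IES-R and HADS, months 4 and 6 | Yes | Yes |
| Reporting of serious events | To end of study | To end of study |

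The first, second and fourth rows differ by arm, and they do not all point the same way. The month 6 visit gives the late arm more opportunity. The observed session gives the early arm more, and so do the ICU-VR items if they are asked before month 6.

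**Step 2. Psychological symptoms**

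IES-R and HADS are completed at month 4, one month after early ICU-VR, and again at month 6. In the late arm the month 6 questionnaire is sent at "6 months (prior to the second outpatient clinic visit for patients in the late intervention group", so that visit cannot influence it. Worsening PTSD, anxiety or depression symptoms are therefore measured evenly. They are measured as outcomes, however. Nothing in the harms section says whether or when a worsened score becomes an adverse event with an onset date and follow-up.

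**Step 3. What decides the size (assumed inputs only)**

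Assume the same true risk in both arms. Let c be the share of events captured through contact common to both arms. Let v be the share of the remaining events picked up at the late-arm visit, and w the share of the remaining events picked up only in the early arm (session or ICU-VR items). The ratio of recorded events, early to late, is

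R = [1 − (1 − c)(1 − w)] / [1 − (1 − c)(1 − v)].

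- If v = w, R = 1.00.
- With w = 0 and c = 0.8: v = 0.3 gives 0.80/0.86 = 0.93, and v = 0.6 gives 0.80/0.92 = 0.87.
- With w = 0 and c = 0.5: v = 0.3 gives 0.50/0.65 = 0.77, and v = 0.6 gives 0.50/0.80 = 0.625.
- With v = 0 the ratios invert. For c = 0.5, w = 0.3 gives 0.65/0.50 = 1.30, and w = 0.6 gives 0.80/0.50 = 1.60.

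In events, 80 patients allocated 1:1 are 40 per arm. An assumed true risk of 10% gives 40 × 0.10 = 4 events per arm. With c = 0.5 and w = 0, the early arm records 4 × 0.50 = 2.0. The late arm records 4 × 0.65 = 2.6 (v = 0.3) or 4 × 0.80 = 3.2 (v = 0.6).

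None of c, v, w or the 10% comes from the article. The formula shows only that the bias vanishes when the arm-specific routes balance or add nothing, and that its sign depends on which of v and w is larger.

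**The case against.** The strongest reply has four parts.

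- **Article condensation.** A journal article shortens the full protocol, and the wording of adverse-event elicitation is commonly left to that document. This stands in part. The wording of an enquiry is no finding, and a participant report may well be a prompted one. The point rests on what the article does state: a capture rule, combined with a visit that one arm has and the other does not. If the full protocol (version 1.3) already specifies an equal enquiry, a one-line confirmation settles the matter.
- **The most plausible harm is already measured.** This stands for symptoms covered by IES-R and HADS. It does not cover events outside those scales, or the handling of worsened scores as adverse events.
- **No between-arm adverse-event analysis is planned.** Correct: the objectives, outcomes and statistical methods contain none. The concern applies to any summary of events by arm.
- **No event enquiry is stated at the month 6 visit either.** Correct, so that visit may add little. This is the case v = 0.

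A reader might go further and infer that delayed harm from early ICU-VR is in fact under-recorded relative to the control. The documents do not support that. It would require the month 6 visit to yield events that the common contact missed, and to outweigh closer observation of the early arm at month 3. Open-label recipients may also attribute and report more. Nor do the documents show that a real excess would be hidden. Such a result would come entirely from the capture rates one chose to assume.

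**Conclusion.** The point holds as a risk of ascertainment bias. The stated capture rule depends on contact, contact differs by arm in the only period with an untreated control, and no equal enquiry is stated. Adverse-event counts for months 3 to 6 may therefore be biased between arms.

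The size is unknown. Under the assumptions shown, the recorded ratio with equal true risk runs from 1.00 down to 0.625 if only the late-arm visit adds capture, and up to 1.60 if only the early-arm routes do. The direction is not established. The gap is confined to events outside IES-R and HADS and to whether worsening on those scales is treated as an adverse event. Treatment, sample size and the primary analysis are unaffected.

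**What to change.** In the harms section:

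- State one identical open adverse-event question, asked in both arms at the existing questionnaire calls of months 4, 6, 7 and 12. In the late arm, ask it at month 6 before the second clinic visit.
- Record the onset date of each event relative to ICU-VR.
- Base any between-arm summary for months 3 to 6 on these solicited events. List events seen at visits or during ICU-VR sessions separately.
- Say how a worsened IES-R or HADS score is handled for adverse-event recording.

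The trial status section says that recruitment has ended and data collection continues, so the question can be added only at contacts still to come. For contacts already past, report adverse events by how they were captured and do not pool them with solicited events.

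The cost is one scripted question on calls already made and one added field on the case report form. The downside is small: more minor events to record and follow.
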